##### Mixed methods integration

The comparison and integration of findings from quantitative and qualitative data will be used to better understand metrics for reach, implementation fidelity, and maintenance. Merging of data will occur through triangulation which is often used to display findings emerging from different data types to gain a better understanding or a more complete picture [85]. We will develop a matrix to assess whether findings from quantitative and qualitative data converge (provide the same answer), contradict each other (dissonance), or are salient [86]. Results from our qualitative analysis will also be embedded within the quantitative data to provide context for outcomes (e.g., how, why?) using a complementary approach.

### Power analysis

All power analyses were conducted with G*Power v. 3.1 [87], using different potential sample and effect sizes, assuming nine CSC sites, and three waves to estimate the power to detect effects. Power estimations for Aim 1 focused on engagement primary outcomes. Using the design effect approach in the Shiny-CRT power estimation application [88], a sample size of 450 participants, with an effect size of 0.5, at a 2-sided alpha level of 0.025, and assuming an ICC in each period of 0.01, the estimated power to detect a significant difference between ACC and FAMES conditions for the primary outcome of engagement would exceed 85%. For specific to Aim 2, power analyses assumed a conservative *R*^2^ value of 0.10 for predicting engagement from seven Block 1 control variables. Based on a sample of 225 family member participants in the FAMES condition, at a two-sided alpha level of 0.05, estimated power would be 98% when assessing whether *R*^2^ differed significantly from zero. With the addition of three Block 2 mediator variables (change in inventory scores), if *R*^2^ was to increase to 0.20 so that the change in *R*^2^ is 0.10, with an adjustment to the two-sided alpha to 0.025 due to multiple hypothesis tests and potential correlation between Block 1 and 2 predictors, and an adjusted effect size for Block 2 change given Block 1 variables [89] power would increase to 99% to detect a significant change in *R*^2^. Estimated power to achieve significant differences in implementation outcomes (i.e., pre- and post-change in knowledge) assumed a standardized mean difference of 0.60. Based on a sample of 20 family peer and provider participants, at a one-sided alpha level of 0.05, and a correlation among repeated measures of 0.50, estimated power would be 83% to establish significant change in knowledge. As such, this study is sufficiently powered (> 80% power) to detect meaningful differences in engagement outcomes, mediation effects, and knowledge, with adjustments for clustering and the stepped-wedge design structure.

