### Randomization

CSC programs will be randomized to one of three waves with different study start times offset by three months (Fig. 2). A two-stage stratified randomization procedure will be applied to account for differences in site size (large vs. small), using a median split by site panel size to designate sites as large or small. This block randomization method stratified by the size of the CSC program will ensure small and large sites have a balanced opportunity to receive the innovation at any point in the study timeline. To reduce the possibility of implementation contamination, study staff will perform each randomization incrementally at six months prior to the start date for the next wave.

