**Fig. 2 Fig2:**

The modified stepped-wedge randomized trial across three waves. CSC, Coordinated Specialty Care; ACC, Attention Control Condition; FAMES, Family Motivational Engagement Strategy; CFI, Cultural Formulation Interview

After site randomization, each CSC program will be allotted 18 months to recruit participant dyads to receive the ACC during the control phase, after which sites will participate in a three-month pre-implementation phase to commence training of family peers, program directors, and family education and support providers, followed by a 30-month active implementation phase to recruit a new cohort of participant dyads to receive FAMES (Fig. 2).

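### The stated Aim 1 power above 85% does not fit the trial's own calendar: ACC and FAMES recruit side by side for only three months, and the planned wave term does not adjust for time

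*Protocol article*

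**What the plan says.** The Power analysis section of the protocol article works from "a sample size of 450 participants, with an effect size of 0.5". The test is two-sided at 0.025 with a within-period ICC of 0.01, "assuming nine CSC sites, and three waves to estimate the power to detect effects". The method is described as "Using the design effect approach in the Shiny-CRT power estimation application". The result is that "the estimated power to detect a significant difference between ACC and FAMES conditions for the primary outcome of engagement would exceed 85" per cent. The section closes by calling the study sufficiently powered, above 80%, for engagement among other outcomes, "with adjustments for clustering and the stepped-wedge design structure".

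The calendar is given elsewhere. Under Randomization, "CSC programs will be randomized to one of three waves with different study start times offset by three months". In the text with Fig. 2, "each CSC program will be allotted 18 months to recruit participant dyads to receive the ACC during the control phase". A three-month pre-implementation phase follows, then 30 months of FAMES recruitment. The section on participant dyads sets 225 dyads per condition.

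The Aim 1 analysis section specifies a mixed model with a random site effect, a fixed effect for phase (ACC or FAMES) and a fixed effect for wave. The wave effect is there to guard against confounding by time. No calendar-period effect is named.

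**The concern.** In a stepped wedge, every site moves from control to intervention, so the effect can be separated from secular change only where some sites are still on control while others have crossed over. Here each site follows the same 18/3/30-month pattern, shifted by three or six months. The control phase is long compared with the shift, so nearly all ACC dyads enrol before nearly all FAMES dyads. A power figure said to allow for the stepped-wedge structure implies much more concurrent comparison than this calendar provides.

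This is the trial's primary effectiveness question. If calendar time is adjusted for, the result may well be inconclusive at the assumed effect. If it is not, any change in family engagement over more than four years of recruitment is counted as an effect of FAMES.

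**Working it through.** **Inputs.** From Power analysis: 450 dyads, effect 0.5 SD, two-sided alpha 0.025, ICC 0.01, nine sites, three waves. From Randomization and the Fig. 2 text: 3-month offset and 18/3/30 months. From the dyads section: 225 per condition, so 25 + 25 per site on average. Assumed: three sites per wave, equal site sizes, even accrual, total variance 1, and one engagement outcome per dyad dated by enrolment.

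**Method.** Generalised least squares on site-by-period means. A cell mean with n dyads has variance ICC + (1 − ICC)/n, and two cells of the same site have covariance ICC. SE is the square root of the treatment entry of (X′V⁻¹X)⁻¹. Power ≈ Φ(0.5/SE − 2.241), where 2.241 is the normal quantile for two-sided alpha 0.025. The effect detectable with 85% power is (2.241 + 1.036) × SE.

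**Step 1: the stated figure.** Take nine sites, three sequences and four equal periods, with 450/36 = 12.5 dyads per cell and period effects. SE = 0.1505; 0.5/0.1505 = 3.322; 3.322 − 2.241 = 1.081; power 86.0%. This agrees with the stated result.

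**Step 2: the calendar in study months.**

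| Wave | ACC recruits | Gap | FAMES recruits |
|---|---|---|---|
| 1 | 0–18 | 18–21 | 21–51 |
| 2 | 3–21 | 21–24 | 24–54 |
| 3 | 6–24 | 24–27 | 27–57 |

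Both conditions recruit at once only in months 21–24: wave 1 on FAMES and wave 3 on ACC, with wave 2 in its gap. FAMES dyads in that window: 75 × 3/30 = 7.5. ACC dyads: 75 × 3/18 = 12.5. Together 20 of 450, or 4%.

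**Step 3: power on that calendar, same inputs, phase and wave terms in every model.**

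| Time term added | SE | Power | Detectable effect at 85% |
|---|---|---|---|
| 3-month periods | 0.477 | 12% | 1.56 |
| 6-month periods | 0.413 | 15% | 1.35 |
| 12-month periods | 0.384 | 17% | 1.26 |
| 9-month periods | 0.278 | 33% | 0.91 |
| Linear calendar trend | 0.202 | about 60% | 0.66 |
| None (model as written) | 0.094 | 99.9% | 0.31 |

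First row worked: 0.5/0.477 = 1.048; 1.048 − 2.241 = −1.193; Φ = 0.12. The 9-month bins do better only because their boundaries pool non-concurrent ACC and FAMES months into one period.

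**Step 4: sensitivity.** Without the wave term, 3-month periods give 12.2%. With ICC 0.05 and the wave term kept, they give 12.1%. Ending recruitment at month 54 (May 2025 to October 2029, Trial status) leaves the 12.2% unchanged.

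**Step 5: why wave does not stand in for time.** A site belongs to one wave throughout. The wave effect therefore shifts that site's ACC and FAMES means equally and drops out of the within-site contrast. The SE with phase and wave is 0.094, the same as with phase alone.

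**The case against.** The best counter-argument is that the planned model contains no calendar-period term, and under it power on the actual calendar is 99.9%, so the statement that power exceeds 85% is literally true. That stands as arithmetic. It does not rescue the claim, because the power is said to include adjustment for the stepped-wedge structure and the wave term is meant to deal with time. Without a working time term the analysis is a before-after comparison.

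Second, the layout entered in the power software is not reported. The four-period wedge is inferred because it returns 86.0%. Parallel-cluster design effects also satisfy the statement (99.4% with 25 per cluster, 98.2% with 50). So the stated figure is consistent with a textbook wedge, and no more than that can be said. The mismatch with the calendar does not depend on knowing the input.

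Third, Table 1 collects engagement monthly, so ACC dyads enrolled near month 24 are still observed after more sites have crossed over. If monthly values were modelled with month or quarter effects (no wave term, constant effect, an assumed within-dyad correlation of 0.3 to 0.8), power would be about 29 to 45% with three months of data per dyad and 67 to 85% with six. This also stands. Table 1 equally supports one total attendance rate per family, and the article does not say which is modelled.

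A reader might infer that the trial simply has 12 to 17% power. The documents do not support that as a flat statement: it requires categorical 3-, 6- or 12-month periods and one outcome per dyad.

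**Conclusion.** The concern holds in a conditional form. The figure above 85% is consistent with a textbook stepped wedge but not with the schedule the article describes. With one outcome per dyad, no time-adjusted analysis examined reaches it: about 12 to 17% with 3-, 6- or 12-month effects, about 33% with 9-month bins, and about 60% with a linear trend. Only the model as written exceeds it on this calendar, and that model does not adjust the ACC-to-FAMES contrast for time.

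The size rests on three equal sites per wave, even accrual and a normal approximation. Fig. 2 is not available, but the calendar follows from the text. Modelling monthly values would raise the figures, at the most favourable assumptions to about the stated level.

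It would also go too far to conclude that the crossovers must be re-spaced. That would be a redesign with its own trade-offs, and correcting the power statement does not require it.

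**What to change.** 1. In the Aim 1 analysis section, add a calendar-time term to the primary model and state its form (period length or trend). Wave may stay, but should not be described as the control for time.
2. State whether the engagement outcome is one value per family or monthly values, since power depends heavily on this.
3. Recompute Aim 1 power and the detectable effect for the 18/3/30-month calendar with the 3-month offset under that model, and report the period layout and cell sizes used.
4. Replace the above-85% statement, and the closing above-80% statement as it applies to engagement, with the result.

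The cost is text and one recalculation, with no change to recruitment, sites or schedule. The downside is that the stated power will probably be less favourable.

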### Study sites

Nine CSC programs geographically distributed throughout the USA will serve as study sites. The geographical location of sites represents both rural and urban communities, hospital-based and community-based programs, and has a combined ethnoracially diverse set of families. CSC programs are generally comprised of a program director, family education and support specialist, peer support specialist, case manager, education and employment specialist, and a medical prescriber. Nine part-time family peers, with lived experience of having a loved one who has experienced psychosis, will be hired by each CSC at least three months prior to the pre-implementation phase. Across the nine CSC sites, the following team roles will be consented to participate in study activities: Program directors/supervisors (*n* = 4), family education and support providers (*n* = 4), program director/family education and support provider (*n* = 4), and family peers (*n* = 9).

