#### Aim 2: Assess whether target mechanisms mediate FAMES engagement

##### Quantitative data analysis

To examine whether potential mechanisms (connectedness, self-efficacy, and motivation) mediate engagement in FAMES, hierarchical linear regression (HLR) will be used, with predictor variables entered in sequential steps. Demographic variables (age, gender, biological sex, race, ethnicity, years of education, employment status, marital status, clinic), will be entered in Block 1, followed by changes in mediator variables in Block 2. The unique contribution of each mediator will be assessed using changes in adjusted R2, and only significant predictors will be retained in the final models. Regression assumptions will be evaluated using variance inflation factors (multicollinearity) and Durbin-Watson statistics (independence of errors). To explore potential nonlinearity, alternative specifications such as interaction terms or polynomial transformations may be tested.

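### The 98% power for the Aim 2 Block 1 test is computed for seven control variables, but the analysis plan enters nine, including clinic; at the stated R² it is at most about 89% with clinic as a nine-level factor.

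*Protocol article*

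**What the plan says.** All references are to the protocol article.

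- **Power analysis, Aim 2.** The first calculation concerns "predicting engagement from seven Block 1 control variables", with an assumed R² of 0.10. It is "Based on a sample of 225 family member participants in the FAMES condition", at a two-sided alpha of 0.05, and concludes that "estimated power would be 98% when assessing whether" R² differs from zero. A second calculation adds three Block 2 mediators, raises R² from 0.10 to 0.20, lowers alpha to 0.025 and reports 99%.
- **Aim 2, Quantitative data analysis.** "Demographic variables (age, gender, biological sex, race, ethnicity, years of education, employment status, marital status, clinic), will be entered in Block 1". That is nine named variables. Changes in the mediators follow in Block 2.
- **Study sites.** "Nine CSC programs geographically distributed throughout the USA will serve as study sites", so clinic has nine levels.
- **Power analysis, last sentence.** The study is called sufficiently powered (over 80%) for engagement outcomes, mediation effects and knowledge, "with adjustments for clustering and the stepped-wedge design structure".

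**The concern.** Two sections describe the same regression block and disagree on its size. The power of an overall F test depends on its numerator degrees of freedom: for a fixed R², each added term lowers it. Nine variables exceed seven under any coding. Clinic alone, entered as a nominal factor, takes 9 − 1 = 8 degrees of freedom, more than the whole block that was powered. So the 98% does not describe the planned model.

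The closing sentence adds a related difficulty. Only the Aim 1 calculation shows an ICC and a design effect. The Aim 2 calculation works from R², the number of predictors, the sample size and alpha; its only adjustments are to alpha and to the Block 2 effect size. The knowledge calculation works from a standardized difference, 20 participants and a repeated-measures correlation. Neither shows an allowance for clustering or for the stepped-wedge structure. In the Aim 2 model the term that accounts for site is clinic, and a block of seven predictors cannot contain it as a nine-level factor.

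At stake is the accuracy of a published power statement. Sample size and the mediator test do not depend on it.

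**Working it through.** **Inputs.** N = 225, R² = 0.10, alpha = 0.05, seven predictors and stated power 98% (Power analysis); nine named Block 1 variables (Aim 2, Quantitative data analysis); nine sites (Study sites).

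**Method.** Overall F test for a multiple regression with fixed predictors:

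- f² = R²/(1 − R²) = 0.10/0.90 = 0.111
- noncentrality λ = N × f² = 225 × 0.111 = 25
- numerator df = u; denominator df = N − u − 1
- power = P(noncentral F with noncentrality λ exceeds the upper 5% point of the central F)

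**The plan's own figure.** With u = 7 and denominator df 217, power is 96.9% (96.5% if the predictors are treated as random). This is about one point below the stated 98%, which corresponds to about five predictors (98.2%). I treat the figure as reproduced; a gap of that size would not merit comment.

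**The listed block.** The lowest count with clinic as a nominal factor is 8 for clinic plus 8 × 1 for the other eight variables = 16. Race, gender, employment status and marital status can only add to this. The document does not give their category counts, so the rows above 16 are illustrations.

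| Block 1 df | Coding | Denominator df | Power |
|---|---|---|---|
| 7 | as powered | 217 | 96.9% |
| 9 | nine variables, one df each | 215 | 95.4% |
| 16 | clinic 8 df, the others one each | 208 | 89.0% |
| 22 | six further df (assumed) | 202 | 83.0% |
| 24 | eight further df (assumed) | 200 | 81.0% |
| 25 | nine further df (assumed) | 199 | 80.0% |

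With random predictors the 16-df figure is 88.3%.

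**Sensitivity to R².** The table keeps R² at 0.10 while the block grows. To regain 96.9%, R² would have to be about 0.129 at 16 df or 0.144 at 22 df. To reach 98% it would have to be about 0.137 or 0.153.

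**Block 2.** f² = (0.20 − 0.10)/(1 − 0.20) = 0.125, numerator df 3, alpha 0.025. Power is 99.3% at 7 Block 1 df and still 99.2% to 99.3% at 30. With the smaller f² = 0.10/0.90 = 0.111 it is 98.4%. The stated 99% stands.

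**The case against.** The strongest reply is that the document does not fix the Block 1 degrees of freedom. Coding of race, gender, employment and marital status is the kind of detail left to an analysis plan, and even the coding of clinic is not spelled out. This stands in part. A reader might infer that the specified model has 83–89% power, or that it falls below 80%. The document supports neither, because everything under 89% rests on category counts it does not give. It does not rescue seven, however, since nine single-df terms already exceed it. Nine sites have no natural order, so a nominal factor is the ordinary reading of clinic.

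Second, R² = 0.10 was called conservative and was set for seven predictors; adding variables cannot lower the population R², and clinic may explain some of the variation in engagement. This stands as a qualification: the lower figures are conditional on R² = 0.10. But the document offers no larger value for the larger block.

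Third, Block 1 contains only controls. A reader might infer that Aim 2 is underpowered. It is not: the mediator question rests on Block 2, whose power hardly moves.

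Fourth, the closing clause can be read as a loose summary of the study as a whole, with Aim 1 in mind, and clinic as a covariate does address site in the Aim 2 analysis. That is a fair reading of the intent. As written, though, the clause attaches to mediation effects and knowledge too, and neither calculation shows such an adjustment.

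**Conclusion.** Wrong as written, with minor consequence. The count of seven contradicts the nine listed variables, so 98% is not the power of the planned Block 1 test. The loss against the stated figure is about 3 points if every variable takes one degree of freedom (98 − 95.4 = 2.6) and about 9 points if clinic is a nominal factor (98 − 89.0 = 9.0). It is larger if other variables are multi-category. All of this assumes R² = 0.10 and N = 225. On those assumptions power stays above 80% up to 24 degrees of freedom. The Block 2 test is unaffected at about 98–99%, so no conclusion about the adequacy of the sample for the mediator question changes. The adjustment for clustering and stepped-wedge structure is shown for Aim 1 only.

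**What to change.** 1. Make the Block 1 list in the Aim 2 analysis and the count in the Power analysis agree, and state the degrees of freedom used, including how clinic is coded.
2. Restate Block 1 power for that number. If clinic is a factor and R² stays at 0.10, it will be at most about 89%. If a larger R² is assumed for the larger block, say so and give the reason.
3. Confine the closing clause on clustering and stepped-wedge structure to the Aim 1 calculation.

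The cost is a few lines of text and one less favourable figure. Design, sample size, conduct and the Block 2 power statement need no change.

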### Data analysis plan

All analyses will follow an intention-to-treat principle with participant data within clusters analyzed according to the cluster’s randomized crossover time. All quantitative analyses will utilize a type I error rate of *p* < 0.05. Multiple imputation will be used for missing secondary psychological outcomes, with separate imputations conducted by study phase and clinic, incorporating demographic variables to ensure the accuracy of imputed values under the assumption of missing at random. Analyses will be conducted using STATA version 14.2, R statistical software, or the Statistical Package for the Social Sciences (SPSS, version 31.0).

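### The 0.025 level used to power the Aim 2 mediator block is not carried into the Aim 2 analysis, which would judge each of three mediators at p < 0.05

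*Protocol article*

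**What the plan says.** All references are to the Protocol article.

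- **Power analysis, Aim 2, Block 1.** The plan says "power analyses assumed a conservative *R*^2^ value of 0.10 for predicting engagement from seven Block 1 control variables", with 225 family members in the FAMES condition, two-sided alpha 0.05 and stated power of 98%.
- **Power analysis, Aim 2, Block 2.** Three mediator change scores are added, and R² is taken to rise from 0.10 to 0.20. The level for this step is described as follows: "with an adjustment to the two-sided alpha to 0.025 due to multiple hypothesis tests and potential correlation between Block 1 and 2 predictors". The claimed result is that "power would increase to 99% to detect a significant change in *R*^2".
- **Data analysis plan, opening paragraph.** The general level is p < 0.05, in a sentence that opens "All quantitative analyses will utilize a type I error rate of".
- **Data analysis plan, Aim 1.** A Bonferroni correction is specified, and its scope is the primary engagement outcomes.
- **Data analysis plan, Aim 2.** The decision is made mediator by mediator: "The unique contribution of each mediator will be assessed using changes in adjusted R2, and only significant predictors will be retained in the final models". No significance level and no correction are given.
- **Power analysis, closing sentence.** The study is said to have more than 80% power for mediation effects, among others.

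**The concern.** The authors recognised multiplicity in Aim 2 and used a stricter level when planning, but that level never reaches the rule by which results will be judged. A mediator with p = 0.03 is retained under the general rule in the Data analysis plan and fails the level used in the Power analysis. In Aim 1 the two sections do match: its power calculation also uses 0.025, and the analysis text contains a multiplicity correction to go with it. Aim 2 has no such counterpart.

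The test that was powered also differs from the test that decides. The 0.025 and the 99% belong to the change in R² when all three mediators enter together. Naming connectedness, self-efficacy or motivation as a mechanism depends on each one's own test. At stake are the false-positive rate for mechanism claims, the freedom to choose a threshold once p-values are known, and a reader's belief that 99% applies to a single mechanism. The Aim 1 comparison is not touched.

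**Working it through.** **Inputs (Power analysis, Aim 2).** N = 225; seven Block 1 variables; three Block 2 mediators; R² rising from 0.10 to 0.20; alpha 0.025 for the block. From the Data analysis plan: alpha 0.05 for all quantitative analyses.

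**Formula.** Fixed-model multiple regression: noncentral F with λ = f² × N, numerator df u = number of predictors tested, denominator df v = N − total predictors − 1.

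**1. The plan's own figures.**
- Block 1: f² = 0.10/0.90 = 0.111, u = 7, v = 217, alpha 0.05. Power 96.9%, against the stated 98%; close.
- Block 2, joint: f² = 0.10/0.80 = 0.125, λ = 0.125 × 225 = 28.1, u = 3, v = 225 − 10 − 1 = 214. Power **99.3% at 0.025** and **99.7% at 0.05**. The stated 99% reproduces. With the more cautious f² = 0.10/0.90 it is 98.4% at 0.025.
- The Aim 2 analysis text lists nine Block 1 variables, not seven. With nine, the joint power at 0.025 is still 99.3%.

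**2. Family-wise error of three mediator tests, all null.** If independent, it is 1 − (1 − α)³.
- α = 0.05: 1 − 0.95³ = **14.3%**.
- α = 0.025: 1 − 0.975³ = **7.3%**.

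For two-sided normal tests with equal pairwise correlation (an assumption; the plan gives no correlation):

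| Level per test | Independent | Correlation 0.5 | Correlation 0.7 |
|---|---|---|---|
| 0.05 | 14.3% | 12.5% | 10.9% |
| 0.025 | 7.3% | 6.5% | 5.7% |

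Used without a preceding joint test, neither level holds 5% across three mediators in these cases.

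**3. Power for one mediator.** The plan states none, so a unique contribution must be assumed. With u = 1, v = 214, full-model R² = 0.20 and f² = ΔR²/0.80:

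| Unique ΔR² (assumed) | f² | λ | Power at 0.05 | Power at 0.025 |
|---|---|---|---|---|
| 0.033 (0.10 split equally) | 0.0417 | 9.4 | 86% | **79%** |
| 0.02 | 0.025 | 5.6 | 66% | **55%** |

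**4. Does a joint gate at 0.05 followed by 0.025 per mediator control the family-wise error?**
- All three null: a false claim requires the gate to be passed, so at most 5%.
- Two null: at most 2 × 0.025 = 5%.
- One null: at most 2.5%.

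It does, for three mediators and for any correlation between them.

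**The case against.** The strongest reply is that the plan already has a rule. The general statement covers every quantitative analysis, so p = 0.03 counts as significant, and the 0.025 is only a planning assumption. A planning alpha stricter than the analysis alpha understates power, so nothing is inflated and N stands. The reasons given for 0.025 also include correlation between the two blocks, and the multiple tests meant may be the two R² tests rather than the three mediators. Correction for secondary mechanism tests is a choice often left to an analysis plan that is not shown here.

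Much of this stands, and it rules out three stronger readings that a reader might infer:

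- *That a p-value between 0.025 and 0.05 has no verdict at all.* The general rule gives it one. The defect is two conflicting levels, not an absent one.
- *That the individual mediator tests were powered at 0.025, or that the 99% is wrong.* The 0.025 was attached to the joint change in R², and 99% is right for that test.
- *That the claim of more than 80% power for mediation is shown to fail.* For a single mediator it depends on an unstated split of the effect. Under an equal split it misses by about one point at 0.025 and reaches 86% at 0.05.

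The reply does not remove the mismatch itself. The document states a level in both places, gives multiplicity as one reason for the stricter one, and applies no adjustment where mediators are kept or dropped. That is a conflict within the text, not a detail left for later. The 11–14% error rates do require all three mediators to be null, and the general 5% is not worded as a family-wise guarantee for Aim 2.

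**Conclusion.** The point holds as an inconsistency in the Aim 2 decision rule. The joint block test is planned at 0.025, partly for multiplicity, while the analysis text would judge each mediator at 0.05 without adjustment. Following the analysis text, the chance of naming at least one false mechanism is 14.3% for independent tests and 10.9–12.5% for correlations of 0.7 to 0.5, in each case with all three null.

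The power statement and the sample size are sound for the joint test. What is missing is any power for the tests that actually select a mechanism. The illustrative values of 79% and 55% at 0.025 rest on assumed unique contributions of 0.033 and 0.02, neither of which the document gives. This affects secondary mechanism claims only and should be settled before Aim 2 results are seen. According to the Trial status section, recruitment is expected to run to October 2029.

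**What to change.** State one Aim 2 rule, in the same terms, in the opening of the Data analysis plan, in the Aim 2 analysis and in the Power analysis:

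1. Test Block 2 jointly with the 3-df F test of the change in R² at 0.05.
2. Only if that is significant, test each of the three mediators at two-sided 0.025. This holds the family-wise error at 5% for three mediators, as shown in step 4 of the working. A stricter first step such as Holm's 0.05/3 = 0.0167 is not needed after the joint test.
3. Exempt Aim 2 from the blanket p < 0.05 statement.
4. Say that the 99% refers to the joint test only, and add that power for a single mediator at 0.025 would be about 79% if the 0.10 were split equally (an assumption), and 55% for a unique R² of 0.02.

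The cost is wording in three places and a less favourable power statement for individual mediators. No further data or participants are needed.

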### Research objectives and aims

Informed by the Health Equity Implementation Framework which explicitly focuses on equitable implementation of interventions to address inequities in care [45], the overarching goal of this study is to improve family engagement in CSC and address disparities in engagement. To accomplish this, the present study has three aims: (1) to evaluate whether integrating FAMES improves family member/support person engagement in CSC compared to an attention control condition (ACC); (2) to examine whether target mechanisms of connectedness, self-efficacy, and motivation mediate FAMES engagement among family members/support persons; and (3) to assess the impact of FAMES on reach, adoption, implementation, and maintenance using a concurrent mixed-methods approach.

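### The 99% power for Aim 2 belongs to the joint test of three mediators, but the plan judges each mediator separately and gives no power for that

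*Protocol article*

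**What the plan says.** Under Research objectives and aims, Aim 2 is "to examine whether target mechanisms of connectedness, self-efficacy, and motivation mediate FAMES engagement among family members/support persons". Three separate mechanisms are named.

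The Aim 2 analysis section enters demographic variables in Block 1 and changes in the mediators in Block 2. It then says: "The unique contribution of each mediator will be assessed using changes in adjusted R2". Only predictors that reach significance stay in the final models.

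The Power analysis section starts from an R² of 0.10 "for predicting engagement from seven Block 1 control variables". The sample is stated as "Based on a sample of 225 family member participants in the FAMES condition". It continues "With the addition of three Block 2 mediator variables (change in inventory scores"), which take R² to 0.20, a gain of 0.10, at a two-sided alpha of 0.025, and reports that "power would increase to 99% to detect a significant change in *R*^2". The section closes by saying that "this study is sufficiently powered (> 80% power) to detect meaningful differences in engagement outcomes, mediation effects, and knowledge".

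**The concern.** The power calculation and the planned analysis answer different questions. The calculation asks whether the three mediators as a set add to the prediction of engagement. The analysis asks whether each mediator adds something given the other two, and it drops those that are not significant. The set shares one R² gain of 0.10, so no more than part of it is available to each mediator unless one carries everything. If the mediators are positively correlated, some of the gain belongs to none of them uniquely.

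The retention rule makes this matter. A mechanism tested with 30% to 70% power will often fall out of the final model. Set against a published 99%, or more than 80% for mediation effects, its absence could be taken as evidence that the mechanism plays no part. Aim 2 exists to learn about connectedness, self-efficacy and motivation individually, so the power that matters to its reader is the one not given.

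**Working it through.** **Inputs from the Power analysis section.** N = 225; Block 1 with 7 predictors and R² = 0.10; Block 2 adds 3 predictors; full-model R² = 0.20; alpha 0.025 for Block 2. The Data analysis plan section sets 0.05 as the general type I error rate, so both levels are shown.

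**Inputs not in the document (assumptions).** How the 0.10 divides among the mediators, and their pairwise correlation r.

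**Method.** Noncentral F test for an increase in R²: f² = ΔR² / (1 − full R²), noncentrality λ = f² × N, numerator df = number of predictors tested, denominator df = 225 − 10 − 1 = 214.

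**Step 1: the plan's own figure.** f² = 0.10 / 0.80 = 0.125; λ = 0.125 × 225 = 28.1; df 3 and 214; alpha 0.025. Power = 99.3%, so the stated 99% reproduces as the joint test. (With f² = 0.10 / 0.90 = 0.111 it is 98.4%.)

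**Step 2: one mediator given the other two, uncorrelated and equal.** Unique ΔR² = 0.10 / 3 = 0.0333; f² = 0.0333 / 0.80 = 0.0417; λ = 9.375; df 1 and 214. Power = 78.9% at alpha 0.025 and 86.2% at alpha 0.05.

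**Step 3: equal coefficients, common pairwise correlation r.** Hold the joint gain at 0.10. Each mediator's unique share is then

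u = [0.10 / (3 + 6r)] × [1 − 2r² / (1 + r)].

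At r = 0.3, for example, u = (0.10 / 4.8) × (1 − 0.18 / 1.3) = 0.0179, and λ = (0.0179 / 0.80) × 225 = 5.05.

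| r | unique R² | power, alpha 0.025 | power, alpha 0.05 |
|---|---|---|---|
| 0 | 0.0333 | 79% | 86% |
| 0.1 | 0.0273 | 70% | 79% |
| 0.3 | 0.0179 | 50% | 61% |
| 0.5 | 0.0111 | 31% | 42% |
| 0.7 | 0.0059 | 17% | 25% |

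**Step 4: unequal split, uncorrelated, alpha 0.025.** Shares of 0.05, 0.03 and 0.02 give 93%, 74% and 55%.

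**Step 5: unique R² needed for 80% power.** At alpha 0.025 it is 0.0342, and 3 × 0.0342 = 0.103, more than the 0.10 assumed. At alpha 0.05 it is 0.0282, and 3 × 0.0282 = 0.085, less than 0.10. Without suppression (mediators that predict better together than the sum of their separate contributions), unique shares cannot add up to more than the joint gain.

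**Sensitivity.** Raising the total number of predictors from 10 to 23, for instance by coding clinic and demographic categories as indicators, leaves the joint figure at 99.3% and the equal-split figure at 78.9%.

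**The case against.** The strongest reply is that the 99% is no error. The Power analysis section says openly that it concerns adding three mediators and detecting a change in R², and the figure reproduces. That stands: this is a mismatch between power calculation and analysis, not a miscalculation.

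A second reply is that the per-mediator figures need assumptions the document does not make. That also stands. A reader might infer from the 79% that no mediator can do better. The documents do not support that: a mediator with a unique R² of 0.05 has 93% power at alpha 0.025, and one carrying the whole 0.10 would exceed 99%. Nor does correlation in general bring power to 30–50%; that range belongs to r of about 0.5 to 0.3, and at r = 0.1 power is 70%.

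A third reply concerns alpha. The 0.025 is attached to the Block 2 change in R², and the Aim 2 analysis section gives no level for single mediators. At the general 0.05, all three can exceed 80% if they are nearly uncorrelated (86% at r = 0). This limits the claim that all three cannot reach 80% to alpha 0.025. It does not rescue the protocol's statement, because with equal coefficients power is already 79% at r = 0.1. The mediators are three self-report change scores from the same family members over the same months, so zero correlation is the favourable case.

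Finally, a change in adjusted R² is not itself a significance test, and Block 2 is entered as a block. But keeping only significant predictors requires a test of each one. The document does not say that a non-significant mediator will be read as an absent mechanism; that is a risk of interpretation, not a stated plan.

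**Conclusion.** The point holds as a mismatch between what was powered and what will be inferred. The 99% is right for the joint Block 2 test. The closing claim of more than 80% power for mediation effects is not supported for individual mechanisms, because no such power is given and the document's inputs do not determine it.

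Under equal coefficients, per-mediator power runs from 79% (r = 0) to 31% (r = 0.5) at alpha 0.025, and from 86% to 42% at alpha 0.05. These figures rest on the assumed split and correlations. The statement that all three mediators cannot reach 80% needs neither assumption, only alpha 0.025, the document's R² values and no suppression.

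**What to change.** In the Power analysis section, say that the 99% is the power of the joint 3-df Block 2 test, and limit the claim of more than 80% power for mediation effects to that test. Next to it, give per-mediator power as a range under a stated split, correlation and alpha, with the unique R² detectable at 80% power: 0.034 at alpha 0.025 and 0.028 at alpha 0.05. State which alpha applies to the individual mediators.

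In the Aim 2 analysis section, report all three mediator coefficients with confidence intervals from the full Block 2 model, not only the significant ones, and say that a non-significant mediator will not be read as absence of that mechanism. Making the joint F test the only Aim 2 hypothesis test is not required; since the aim names three mechanisms, that choice is debatable.

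The cost is wording in two sections, with no added participants or data. The downside is a less favourable stated power for individual mechanisms.
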